## Abstract

Introduction: Virtually all adults in aged care facilities are frail, a condition which contributes to falls, cognitive decline, hospitalisation, and mortality. Polypharmacy, malnutrition, sedentariness, and sarcopenia are risk factors amenable to intervention. The Asia–Pacific Frailty Management Guidelines recommend anabolic exercise and the optimisation of medications and nutrition. However, no study has evaluated this best practice intervention triad in aged care. Methods: The Frailty Reduction via the Implementation of Exercise, Nutrition, and Deprescribing (FRIEND) Trial (ANZCTR No.ACTRN12622000926730p) is a staged 6-month translational trial evaluating resident outcomes, staff/caregiver knowledge, and institutional implementation in a Townsville aged care facility. Residents received high-intensity resistance exercise and balance training and medication and nutrition optimisation co-implemented by investigators (exercise physiologist, geriatrician, pharmacist, and nutritionist) and facility staff. Staff and caregivers completed comprehensive education modules and training. We report the trial protocol and recruitment results. Results: 29 residents (21 female, age: 88.6 ± 6.3 years) were recruited. At baseline, the residents were frail (frailty scale nursing home (FRAIL-NH); 6.3 ± 2.4/14), cognitively impaired (Montreal Cognitive Assessment; 13.8 ± 6.8/30), functionally impaired (Short Physical Performance Battery; 4.9 ± 3.1/12, 6 min walk distance; 222.2 ± 104.4 m), and were prescribed numerous medications (15.5 ± 5.9). Two residents died and one withdrew before the intervention’s commencement. Thirty family members and 19 staff (carers, allied health assistants, nurse managers, registered nurses, lifestyle–leisure officers, kitchen/hospitality staff, and senior leadership) were recruited to receive frailty education modules. Conclusions: The FRIEND trial is currently being implemented with results expected in mid-2024. This is the first trial to evaluate the implementation of the best practice frailty guidelines including anabolic exercise and medication/nutritional optimisation in residential aged care.

## 1. Introduction

Frailty is the most significant challenge to “ageing well” in Australia and affects virtually all older adults living within residential aged care facilities* [1]. Frailty reduces independence and quality of life and increases the risk of disability, falls, hospitalisation, and premature mortality with care costs doubling for every incremental increase in frailty [2,3]. Importantly, frailty is not an inevitable part of ageing. Instead, sarcopenia, undernutrition, decreased physical activity, chronic disease, and polypharmacy all contribute to frailty and are modifiable with appropriate treatment [2,4]. These treatments, backed by decades of clinical research and guidelines including the Asia–Pacific Clinical Guidelines for Frailty, include anabolic exercise, dietary fortification, and deprescription of inappropriate medications [2,5,6]. The formula is simple, yet this holistic approach to treatment has yet to become standard practice in residential aged care.

While nutritional or deprescribing initiatives in residential aged care facilities (RACFs) have been introduced in some, many barriers exist to sustainable implementation [7,8,9,10,11,12,13,14,15], and robust anabolic (resistance) exercise is virtually absent in this setting, particularly for those with both cognitive impairment and frailty [16]. Moderate-to-high-intensity progressive resistance training (PRT) has been shown to be superior to low-intensity resistance exercise for virtually every outcome targeted [17,18]. However, there is a substantial gap between this evidence and clinical practice due to misplaced fear of robust strength training and a lack of access to appropriate equipment and training protocols. Furthermore, implementing these interventions in isolation without fidelity to the guidelines represents a sub-optimal quality of care [19] which results in a sub-optimal quality of life [20,21,22,23,24] for the most vulnerable older adults. Thus, aged care interventions must not only be holistic to effectively treat frailty but also be implemented sustainably for long-term benefits in RACFs by equipping the sector with the knowledge and resources required.

The Frailty Reduction via the Implementation of Exercise, Nutrition and Deprescribing (FRIEND) Trial is the first study to fully implement these three components into one program in an RACF through co-implementation with facility staff. Furthermore, to increase sustainability in the long-term, the FRIEND trial will provide comprehensive education for staff, residents, and caregivers about the rationale and provision of evidence-based frailty assessment and treatment to improve outcomes for the most vulnerable in aged care.

### 1.1. Aim

The aim of the FRIEND trial was to establish integrated processes and pathways within a residential aged care facility that enable the early identification and effective reduction in frailty in residents with mild cognitive impairment (MCI) or dementia.

### 1.2. Research Objectives

#### 1.2.1. Primary Objectives

Effectiveness: To evaluate the impact of the implementation as assessed by measures of clinical outcomes and measures of experience of care.

Implementation: To examine the implementation outcomes including acceptability, adoption, knowledge transfer and fidelity, influences on uptake, integration, routinisation (structural-, organisational-, provider-, patient-, and innovation-level factors), and cost.

#### 1.2.2. Secondary Objective

The secondary objective was to establish mechanisms for the sustained implementation of the FRIEND trial within the residential aged care facility, as well as wide dissemination and implementation into other aged care facilities.

## 2. Methods

### 2.1. Study Design

The FRIEND trial (ANZCTR Registration No.: ACTRN12622000926730p [25]) was a staged 6-month, single-group pilot implementation research trial employing a mixed-methods research design to evaluate the process and impact of the implementation of best practice frailty management guidelines [2] for the FRIEND trial in the Good Shepard Home (TGSH) residential aged care facility (RACF), in Townsville, Australia. The trial received ethics approval from the University of Sydney Human Research Ethics Committee 25 July 2022 (HREC No: 2022/343) and reciprocal approval by James Cook University HREC (No C41, 23 September 2022) and TGSH board. The FRIEND trial was funded by the Dementia Centre for Research Collaboration (DCRC) ‘Implementing Research Evidence into Practice Grant’ and the James Cook University Philanthropic Chiropractic Research Fund.

### 2.2. Study Population

Participants for FRIEND consisted of aged care residents from three units within TGSH, their caregivers from the community, and staff with diverse roles from the facility including nurses, an exercise physiologist (AEP), care staff, allied health assistants, lifestyle–leisure officers, kitchen staff, and executive leadership including the Director of Care (DOC) and Chief Executive Officer (CEO).

### 2.3. Eligibility Criteria

#### 2.3.1. Aged Care Residents

Inclusion criteria: Men and women, age 60 or above, presence of cognitive impairment or dementia (Montreal Cognitive Assessment (MoCA) score < 26/30), presence of frailty (frailty status FRAIL-NH scale score > 1/14), able to understand written and spoken English. Exclusion criteria: Have permanent medical contraindications to the planned exercise due to unstable or terminal disease, unable to speak or understand instructions provided in English language, bed-bound, planning to relocate to a different area within the facility, or to a different facility within 7 months of trial enrolment.

#### 2.3.2. Family Member/Informal Caregivers of Participating Residents

Inclusion criteria: Men and women, age 18 or above, able to read and converse in English, able to visit their loved one at TGSH at least monthly throughout the duration of the trial, willing to support their loved one during their participation in the trial by (a) accompanying him/her during the study initial screening visit or connecting via video link or call; (b) attending an educational program (online) relating to the management of frailty and completing a pre- and post-knowledge questionnaire; and (c) attending a monthly 30 min case conference at TGSH or receiving care updates on clinical decisions.

Exclusion criteria: Unable to speak and understand English language at a conversational level.

#### 2.3.3. Staff Members

Inclusion criteria: Men and women, employed by TGSH in a role related to the provision of care for the participating residents, fluent English speaker.

Exclusion criteria: Unable to speak and understand instructions provided in English language.

### 2.4. Recruitment

Aged care residents and their caregivers were provided with information about the FRIEND trial in the form of leaflets and presentations, and facility staff (DOC) approached families to discuss interest in participating. Consent was gained by the resident and caregiver to be contacted by FRIEND investigators to perform baseline screening. Similarly, the staff at the facility who had a direct (i.e., clinical nurse manager) or indirect (i.e., kitchen staff) involvement with the three units selected for resident recruitment were also approached by the DOC, and their information passed onto the study investigators with consent to initiate the screening. The recruitment of all participants occurred between December 2022–March 2023.

### 2.5. Sample Size

The primary study population of interest was residents of TGSH aged care facility who were frail and had mild cognitive impairment (MCI) or dementia. Additionally, we aimed to recruit one family member/informal caregiver of each participating resident and at least 10 staff members from TGSH involved in the care of the participating residents.

The sample size was based on the primary effectiveness outcome of this pilot implementation study, using the nursing home frailty scale (FRAIL-NH scale). We expected residents to naturally become frailer over the course of a year without intervention. A longitudinal study of frail nursing home residents (n = 91) has reported an annual worsening (increased score) of 0.63 points without intervention [26]. In contrast, we hypothesised that our intervention involving progressive resistance and balance training, nutrition optimisation, and the deprescription of potentially inappropriate/unnecessary medications would improve the FRAIL-NH components of fatigue, ambulatory function, transfer function, and weight loss in nursing home residents due to expected improvements in strength, physical function, and walking reported in the literature with similar interventions [27,28,29]. We did not, however, expect our intervention to alter the FRAIL-NH items of incontinence, help with dressing, or the dietary modification/assistance required.

While we anticipated that an improvement in the four modifiable components may represent an increase of up to 4 points on the FRAIL-NH scale, we conservatively estimated that our holistic intervention would lead to an improvement (decreased score) of at least 2 points or one-half of this anticipated improvement in frail residents following 6 months of the staged implementation of all components compared to no change from baseline (again, a conservative estimate compared to Little 2021 [26] which suggested an increase (worsening) of at least +0.63 points would have occurred). Using the baseline standard deviation (SD) of 3.61 points for the FRAIL-NH scale reported by Little et al. [26] in nursing home residents (n = 91), we therefore estimated an improvement of a moderate effect size (Cohen’s d of 0.55). Using a two-tailed matched pairs t-test for our pre–post design with an alpha of 0.05 and beta of 0.2, we calculated that we would need to recruit 28 residents to our study.

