## 3. Baseline Results

### 3.1. Recruitment

The recruitment of the residents, caregivers, and staff began in December 2022 and concluded in March 2023. A total of 29 residents (detailed in a CONSORT flow diagram [44], Figure 2), 19 staff, and 30 caregivers were recruited during this period. All residents (but one) who were screened in the units were eligible and consented to join the trial. One resident withdrew from the trial prior to the completion of the baseline assessment, and a further two residents died (unrelated to the trial, n = 1 influenza-A and respiratory decline, n = 1 terminal dementia) prior to the intervention commencing.

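### The 28 residents to recruit in section 2.5 are really 28 complete pre-post pairs with no allowance for loss; with 26 residents left at the start, power under the plan's own inputs is at most about 77%

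*Protocol article*

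**What the plan says.** Section 2.5 (Sample Size) bases the calculation on the FRAIL-NH scale, the primary effectiveness outcome. The intervention is expected to produce a change that "would lead to an improvement (decreased score) of at least 2 points or one-half of this anticipated improvement in frail residents", set against no change. The spread is taken from an external cohort of nursing home residents: "Using the baseline standard deviation (SD) of 3.61 points for the FRAIL-NH scale". From these two figures, "we therefore estimated an improvement of a moderate effect size (Cohen’s d of 0.55"). The test and error rates follow: "Using a two-tailed matched pairs t-test for our pre–post design with an alpha of 0.05 and beta of 0.2". The result is then worded as a recruitment target: "we calculated that we would need to recruit 28 residents to our study". The section gives no loss rate and no inflation step.

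Section 3.1 (Recruitment) reports the outcome: "A total of 29 residents (detailed in a CONSORT flow diagram [44], Figure 2), 19 staff, and 30 caregivers were recruited during this period". One resident withdrew before completing the baseline assessment, and "a further two residents died" before the intervention started. The Abstract agrees: "Two residents died and one withdrew before the intervention" commenced. The final assessment is at M12 (section 2.7.3 and Table 1).

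**The concern.** A matched-pairs t-test uses only residents who have both a baseline and a final score. The number that such a calculation returns is the number of complete pairs, not the number to enrol. The two coincide only if nobody is lost. That is an unlikely assumption here: mean age is 88.6 years, follow-up runs from M0 to M12, and the Conclusions section itself describes a high risk of premature mortality.

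What is at stake is how the result will be read. A reader who takes section 2.5 at face value will treat the FRAIL-NH comparison as a test with 80% power for a 2-point change. On the article's own recruitment figures that was no longer attainable, under the stated inputs, when the intervention started. A non-significant change could then be given more weight as evidence of no benefit than the design allows.

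**Working it through.** **Inputs from the article.** Mean change 2 points; SD 3.61; d stated as 0.55; two-sided alpha 0.05; power 0.80 (all section 2.5). Recruited 29; lost before the intervention 1 + 2 = 3 (section 3.1, Abstract). Own baseline FRAIL-NH SD 2.4 (Table 2).

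**Method.** Exact power of the paired t-test with n pairs: the noncentral t distribution with n − 1 degrees of freedom and noncentrality d√n, compared with the two-sided 5% critical value.

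**Step 1: reproduce 28.** d = 2/3.61 = 0.554, which the article gives as 0.55.

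| Complete pairs | Power at d = 0.55 | Power at d = 2/3.61 |
|---|---|---|
| 28 | 80.1% | 80.7% |
| 27 | 78.6% | 79.1% |
| 26 | 76.9% | 77.5% |

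For n = 28 at d = 0.55, the noncentrality is 0.55 × √28 = 2.91 and the critical value is 2.052. The smallest n that reaches 80% is 28 for either value of d, so the article's figure is reproduced. A normal approximation would give 26 and a one-sided t-test 22; of the variants tried, only the exact two-sided t-test gives 28. It does so with zero loss.

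**Step 2: pairs still possible.** 29 − 3 = 26. Power is at most 76.9% (77.5% with d unrounded), about 3 points below the stated 80%. With 26 pairs the standardised change detectable with 80% power is 0.57, or 0.57 × 3.61 ≈ 2.06 points.

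**Step 3: further loss to M12.** The text gives no loss rate after the start, so these rates are assumptions.

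| Assumed loss of the 26 | Pairs left | Power at d = 0.55 |
|---|---|---|
| 10% | 23 | 71% |
| 20% | 20 to 21 (26 × 0.8 = 20.8) | 65% to 67% |
| 30% | 18 | 60% |

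With 20 pairs the detectable d at 80% power is 0.66.

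**Step 4: what an allowance would have required.** Recruitment needed to keep 28 pairs is 28/(1 − loss), rounded up: 32 at 10%, 35 at 20%, 40 at 30%. The loss seen before the intervention alone, 3/29 = 10.3%, gives 32.

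**Step 5: dependence on the SD.** Section 2.5 uses a baseline SD where the test needs the SD of the change. The SD of the change is 3.61 × √(2(1 − ρ)), where ρ is the correlation between the two scores; it equals 3.61 only if ρ = 0.5. With 26 pairs and a 2-point change, power is about 63% at ρ = 0.3 and about 94% at ρ = 0.7. If the trial's own baseline SD of 2.4 is used in the same way, d = 2/2.4 = 0.83, 14 pairs suffice, and power with 26 pairs is about 98%.

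**The case against.** The strongest reply is that the practical effect is small and conditional. The drop before treatment is from 80.1% to 76.9%, and the effect size is a rough planning value. If the trial's own SD of 2.4 replaced 3.61, 26 pairs would be ample. The study is a single-group pilot implementation trial, its effectiveness results are labelled preliminary, its Conclusions concede the small sample, and recruitment has closed. All of this stands, and it limits the grade. It does not remove the error: section 2.5 derives a number of pairs and labels it a number to recruit. Nor does the SD of 2.4 prove that power is adequate, because a baseline SD of either size is not the SD of change.

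It might also be said that an article condenses the full plan. That does not help here, because the article states the number and gives it the wrong meaning.

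Three stronger readings are tempting and are not supported:

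- **A survivors-only primary analysis that biases the result towards improvement.** The article names the paired t-test only for sizing. Section 2.10 places the detailed analysis plan in Supplementary Materials, which were not available for this review and may already specify a model for incomplete data and a rule for deaths. No criticism of the analysis method follows.
- **Extrapolating the early loss to M12.** Three events, one of them a withdrawal before baseline was complete, are too few for a projection. Figure 2 is captioned as showing resident flow to the 6-month assessment, and it is missing from the copy reviewed.
- **A miscalculation.** There is none; 28 reproduces exactly.

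**Conclusion.** The point holds as a mislabelled sample size with no allowance for loss. Section 2.5 needs 28 complete pairs; at most 26 are possible. Under the stated inputs (two-sided paired t-test, alpha 0.05, d = 0.55 or 2/3.61) power is therefore at most about 77%, and it falls with each further resident who has no M12 score. The 26-pair figure rests only on numbers in the article. The 60% to 71% range rests on assumed losses of 10% to 30% after the start.

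A reader might infer that the trial's power had collapsed before treatment began. The documents do not support that. The established shortfall is about 3 points, and it concerns the stated power under the stated assumptions, not the actual power, which depends on an SD of change that the article does not give. Severity: should be fixed.

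**What to change.** In section 2.5, or in a note with the results, make three changes:

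1. Say that 28 is the number of residents with both measurements, and that no allowance for loss was made.
2. Restate power and detectable change for the 26 residents who started (76.9% at d = 0.55; detectable d 0.57 at 80% power) and for the number expected to complete M12, using the observed flow to M6. For illustration, 20 completers give 65% power and a detectable d of 0.66.
3. Say that these figures treat the external baseline SD of 3.61 as the SD of change, and set beside them the result with the trial's own baseline SD of 2.4 (about 98% with 26 pairs), noting that neither is an SD of change.

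The cost is a few sentences and a slightly less favourable power figure under the stated inputs. No extra residents and no change to the trial's conduct are needed.

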### 2.6. Screening Procedure

Residents who provided informed consent to participate in the trial, and for whom consent was also attained from their caregiver (where required due to dementia), were scheduled to attend an initial screening visit to confirm their eligibility to participate in the trial. This visit took place at TGSH and lasted approximately 1 h. Information pertaining to demographics, medical history, medications, and restrictive practices as well as screening for the presence of frailty (score > 1/14 for FRAIL-NH) and MCI or dementia (MoCA ≤ 26/30) to determine eligibility was reviewed by the study geriatrician before enrolment. Caregivers and staff who met the eligibility requirements were enrolled once informed consent was gained.

### 2.7. Interventions

The FRIEND trial involved a comprehensive, multi-component intervention aimed at residents, caregivers, and facility staff. Primarily, the FRIEND intervention consisted of implementation of the best practice frailty intervention components for residents which included robust resistance and balance exercise and the optimisation of medications and nutrition. These interventions were co-facilitated throughout the intervention period by FRIEND investigators (inclusive of a geriatrician, AEPs, a nutritionist, and a pharmacist) and facility staff and guided by the development and implementation of comprehensive case conferences and reviews.

To support the successful implementation of these interventions for residents over the long term, the FRIEND intervention also involved comprehensive educational modules tailored primarily to facility staff and also for caregivers and residents in an adapted, briefer format. Details of the resident intervention and educational modules are below.

#### 2.7.1. Best Practice Frailty Interventions for Residents

##### Exercise Component of the FRIEND Intervention

The exercise component of the FRIEND trial aimed to improve muscle strength, balance, and mobility while also benefiting conditions such as cognitive impairment, depression, insomnia, hypertension, cardiovascular disease, and metabolic disorders. Thus, it was designed to also potentially reduce the number of medications or remove potentially harmful medications that residents may have been taking. Exercise can also help improve appetite, which may also contribute to better nutrition and a reduction in frailty.

Residents first underwent a comprehensive physical examination (~30–45 min in length) specifically developed to be conducted by an exercise professional (i.e., AEP) to evaluate readiness to undertake high-intensity progressive resistance training (PRT). The tool evaluated common musculoskeletal deficits and conditions (e.g., joint range limitations, posture, rotator cuff disease), neurological signs and symptoms (including parkinsonism, peripheral sensation, motor weakness), orthostatic blood pressure, and a thorough evaluation of skin integrity and peripheral circulation. The findings of this examination were then used to formulate considerations and modifications to exercise while also contributing to the case conference conducted for each resident.

Following the examination, residents attended up to two resistance and balance exercise training sessions per week on non-consecutive days. The sessions were delivered in a purpose-built gym at TGSH and supervised by an AEP, accompanied by exercise physiology students, and allied health assistants in a ratio of 1:1 to 1:3 depending on the level of cognition and function. The session durations were approximately 60–90 min, with balance exercises performed for the first 5–10 min of the session after pre-measures (blood pressure, heart rate) and PRT performed for the remaining part of the session.

Specific resistance exercises critical for mobility and function were prescribed for the upper and lower body using strength training machines [K400 Keiser pneumatic machines, Keiser Sports Health Equipment, Ltd., Fresno, CA, USA] as well as body weight, ankle cuffs, and free weights, depending on the capacity of each resident. Exercises were prescribed for 3 sets of 8 repetitions at 80% of the resident’s maximal capacity and included bilateral leg press, bilateral knee extension, seated row, and hip abduction. The intensity was increased over the first 2 weeks to approximately 80% of maximal capacity and then progressed throughout the 6-month intervention, guided by daily ratings of perceived exertion (15–18 on the Borg scale) [30], along with one-repetition maximum (1RM) strength testing every 6 sessions to maintain the intensity level at 80% of the current maximum capacity or above.

Balance training exercises aimed at reducing fall risk and improving functional capacity were also prescribed. Exercises included static (narrow, semi-tandem, tandem, one leg stance with/without perturbations) and dynamic balance exercises (heel-to-toe walking with/without perturbations and/or dual-task cognitive tasks) tailored to each resident’s balance ability. The intensity was increased continuously throughout the intervention to ensure the exercises remained challenging.

